### Randomization

Treatment assignments are stored centrally in a secure database at the study data coordinating center in Seattle, Washington. For each recruitment site, we utilize permuted-block randomization to achieve roughly balanced groups. We use random blocks of size 4, 6, 8, or 10 that are not divulged to the research assistants involved in recruitment in order to avoid bias in the recruitment process. Two pre-filled opaque syringes are obtained for every study procedure, one filled with the steroid and the other with the local anesthetic. The randomized treatment assignment is obtained via a password-protected study website by the clinical nurse or assistant not involved with subsequent data collection indicating which syringe should be labeled 'inject' or 'discard'. The clinical nurse or assistant confirms the use of the opaque syringe marked 'inject' by the physician performing the injection. The physician, the research staff conducting follow-up interviews, and the patient are therefore all blinded to treatment received.

### Procedure

The procedure is performed in a fluoroscopy suite under strict aseptic conditions. The patient is placed prone on the procedure table. Standard fluoroscopy is used for localization of the spinal/vertebral level to be treated and needle placement for the injection. Fluoroscopic target identification and needle tip entry into the targeted anatomic space is done using previously described procedural techniques [23]. The skin over the back is prepped and draped in a sterile manner using Betadine or chlorhexidine. Local anesthesia with 0.5%-1% lidocaine is injected in the subcutaneous tissues. The epidural and local anesthetic injections are performed using a 20-25 gauge spinal Quinke or 17-20 gauge Tuohy needle. Appropriate needle tip placement is confirmed by fluoroscopy with the injection of 0.5-1.5 cc of iopamadol, ioxehol or equivalent contrast. A fluoroscopic image is obtained following the injection to demonstrate washout of the contrast. This image is saved in the research file. Practitioners are instructed to choose the injection level (e.g., L5-S1) to correspond with one spinal level below the site of maximal canal stenosis for the interlaminar approach injections and at the root level of the greatest symptoms for transforaminal injections. Once an approach (transforaminal versus interlaminar) is chosen for an individual patient, the approach remains consistent for any repeat procedures throughout the trial.

Epidural steroid injectate is 1-3 ml of 0.25-1% lidocaine followed by 1.5-3 ml of 40 mg/ml triamcinolone (i.e. 60-120 mg triamcinolone) in an opaque syringe. The choice of which steroid to use is at the discretion of the treating physician based on his or her usual clinical practice. Betamethasone (6-12 mg), dexamethasone (8-10 mg) or methylprednisolone (60-120 mg) may also be used. The needles are then removed and the patient taken to the recovery area.

The control procedure is identical to the ESI except that the epidural injectate is 1-3 cc of .25%-1% lidocaine followed by 1.5-3 cc of .25%-1% lidocaine in an opaque syringe. The total volume of injectate is the same for the ESI and the control injection to avoid differential treatment effects based on volume.

### Blinding

Every effort is made to maintain blinding of the patients and evaluators during the course of the trial. All baseline and follow up interviews are conducted by a study research assistant who remains blinded to the randomized assignment of the patient throughout the study. The research assistant also completes assessments of blinding at all follow up time points. All datasets have the randomization code masked until all pre-specified analyses are conducted to ensure that the research team remains unaware of patient assignment. Patients are asked to guess which treatment they actually received at 2 weeks, 5 weeks, and 3 months after the initially randomized injection ("ESI", "local anesthetic", or "don't know") and to provide a reason for and confidence in treatment guesses other than "don't know". Specific instances of un-blinding will be recorded and the study statistician will monitor treatment guesses to diagnose systematic problems with the blinding procedure or over the course of conducting the study. Using Fisher's exact test, we will formally compare treatment guesses between arms 2 weeks after randomization when the study results are reported.

### Analytic approach

We are utilizing "intent-to-treat" [24] analyses for the primary effectiveness evaluation, which evaluates outcomes based on the treatment arm to which individuals are assigned. Crossover is not allowed until after the outcome measures have been collected at the study primary endpoint of 6 weeks; therefore, the primary results will reflect the treatment to which the participant was randomized. The evaluable patient subset is defined as those patients with data available for analysis based on their initially randomized treatment. Consideration of missing data is essential to characterize the potential for selection bias through attrition. Characteristics of patients with missing follow-up data will be compared to those with complete data. In sensitivity analyses, we will impute missing outcome data in multiple ways to assess its impact on the primary analyses.

### Primary analyses

Our primary analysis will evaluate the effect of ESI + local anesthetic compared to local anesthetic alone using repeated measures analysis of covariance (ANCOVA). Each ANCOVA model will adjust for the respective outcomes measured at baseline and a dummy variable indicating study recruitment site. From the ANCOVA models, we will report on the means and standard deviations of six-week outcome measures for each group and an adjusted estimate of the mean difference (95% CI) between groups. We will adjust the primary analysis for important baseline characteristics that, despite randomization, differ between groups and are associated with the outcomes.

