### Baseline and follow up assessments

Patients with spinal stenosis who are being referred for an ESI as part of their treatment plan are invited to participate in this study by the treating physician. Interested patients are then screened for eligibility by the research coordinator at the site. If eligible, the potential participant is asked to participate in the study and to complete the informed consent process. A study physician reviews each potential participant's imaging studies to determine the eligibility criterion of presence of central spinal canal stenosis and to categorize the stenosis as mild, moderate or severe.

Baseline questionnaires assess demographic, clinical, and disease-history information and include patient self-report measures of pain, function, fear avoidance [13], and pain catastrophizing [14]. We also ask patients at baseline about their preferences for assignment to the ESI versus the control intervention, and to rate their expectations of pain relief. All medications used for pain at baseline are documented by medical record review as well as co-morbidities measured by the Charlson Comorbidity index [15].

Our primary outcomes are measures of function and pain. These include the Roland-Morris Disability Questionnaire, a back pain-specific functional status questionnaire adapted from the generic Sickness Impact Profile (SIP). It consists of 24 yes/no items, which represent common dysfunctions in daily activities experienced by patients with low back pain. The other primary outcome measure is pain recorded on an 11-point numerical rating scale(NRS) measuring average leg and back pain (separately) in the past week. The primary outcome measures are completed at 3 days, 14 days, 3 weeks, 6 weeks, and 3, 6 and 12 months post-randomization.

Secondary outcome measures include the Brief Pain Inventory (BPI) Interference scale [16], the Patient Health Questionnaire (PHQ-8)measure of depression [17], Generalized Anxiety Disorder (GAD-7) measure [18], Swiss Spinal Stenosis Questionnaire (SSSQ) [19-21], and the EQ-5D [22]. These are administered at all follow-up time points with the exception that the SSSQ, BPI, PHQ-8, GAD-7 and EQ-5D are not administered at Days 3 and 14.

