### Sample size

Our target is to enroll up to 400 patients with half randomized to ESI + local anesthetic and half to local anesthetic alone. We determined overall sample size based on the primary outcome (Roland Morris Disability Questionnaire) with two subgroup analyses (race: Caucasian/non-Caucasian; approach: interlaminar/transforaminal). We will use ANCOVA as the primary method of analysis with the following parameters: 85% follow-up at 6 weeks; two-sided Type 1 error rate of α = 0.05; and adjustment for recruitment site and the outcome measured at baseline. For the purpose of sample size estimation, we conservatively assume six-week Roland Morris Disability Questionnaire scores will have a standard deviation of 7.5 for each group and a correlation between baseline scores and six-week scores of 0.3. For the combined (n = 400) assessment of ESI + local anesthetic vs. local anesthetic alone, the LESS study has 83% power to detect between-group mean differences as small as 2.25 points on the Roland Morris Disability Questionnaire.

Subgroup analyses were powered to detect clinically meaning differences between treatments *within *each subgroup; we did not power the study for the hypothesis of a larger treatment effect within one subgroup compared to another (e.g. an interaction). We adjusted the overall two-sided Type 1 error rate of α = 0.05 using a Bonferroni correction for two tests of the data. Using ANCOVA methods, a sample size of n = 200 (100 per group) provides 83% power to detect between-group mean differences of 3.25 points on Roland Morris Disability Questionnaire.

While formal interim analyses of treatment effect are not planned for this study, we will generate blinded variance estimates for the primary outcomes measured at 6 weeks after a minimum of 100 patients have been enrolled. Conservative estimates of outcome variance and 6-week retention utilized in the initial design of the study yielded an overall upper-bound sample size of n = 400. Adaptive sample size re-estimation will be conducted to provide more precise overall sample size requirements given the observed variance and retention rate, while maintaining the overall Type 1 error rate and power for the stated effect sizes [30].

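### Chance imbalance between arms decides which extra covariates enter the primary model; the list should be fixed in advance on prognostic grounds

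*Protocol article*

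**What the plan says.** The Primary analyses section of the protocol article first fixes the model: "Each ANCOVA model will adjust for the respective outcomes measured at baseline and a dummy variable indicating study recruitment site". The same paragraph ends with a second, conditional rule: "We will adjust the primary analysis for important baseline characteristics that, despite randomization, differ between groups and are associated with the outcomes". That rule applies to the primary analysis itself and is not presented as a sensitivity analysis.

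The Sample size section rests on the first model only, with "adjustment for recruitment site and the outcome measured at baseline". It claims "83% power to detect between-group mean differences as small as 2.25 points on the Roland Morris Disability Questionnaire".

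The Baseline and follow up assessments section lists many candidate variables, among them fear avoidance, catastrophizing, expectation of pain relief and a comorbidity index. It does not single any out for adjustment. The Blinding section keeps the randomization code masked until the pre-specified analyses are complete.

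**The concern.** Under randomization, a baseline difference between arms arises by chance. The reason to adjust for a variable is that it predicts the outcome, and this can be judged before the trial reports. Making imbalance a condition of entry has two consequences.

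- **Standard error.** The rule removes a covariate's chance contribution mainly in the trials where that contribution is large. In the other trials the residual variance still contains the covariate. The reported standard error is then larger, on average, than the true variability of the estimate, so intervals are too wide and the test is conservative.
- **Lost precision.** A prognostic variable that happens to be balanced is left out, and the precision it would have given is lost.

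There is also a question of control. The final model cannot be known until the arms have been compared. The article does not say which result leads if the fixed and the augmented models disagree.

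**Working it through.** **1. The plan's own figure.** Inputs from the Sample size section: 400 patients, 1:1, 85% follow-up, so 200 × 0.85 = 170 per arm; "scores will have a standard deviation of 7.5 for each group"; "a correlation between baseline scores and six-week scores of 0.3"; "two-sided Type 1 error rate of α = 0.05".

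- Residual SD = 7.5 × √(1 − 0.3²) = 7.155
- SE = 7.155 × √(2/170) = 0.776
- Power = Φ(2.25/0.776 − 1.96) = Φ(0.94) = 82.6%

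This agrees with the stated 83%. That figure therefore belongs to the model with the baseline score (and site), not to a model chosen from the data.

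**2. What a fixed prognostic list could add.** If the listed variables explain a further share *e* of outcome variance, residual SD = 7.5 × √(0.91 − *e*). The values of *e* are assumed.

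- *e* = 0.10: SD 6.750, power 86.7%
- *e* = 0.20: SD 6.319, power 90.7%
- *e* = 0.30: SD 5.858, power 94.3%

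**3. What the stated rule does.** Simulated trials of 340 patients with SD 7.5, r = 0.3 and independent candidate covariates; 20,000 runs under no effect and 10,000 at 2.25 points. Site was left out for simplicity. A candidate entered if its imbalance p-value was below the cut-off shown and its association with outcome had p < 0.05. The number of candidates, their strength and the cut-offs are assumptions, because the article gives none. Simulation error (one standard error) is about √(0.05 × 0.95/20,000) = 0.15 points for size and √(0.83 × 0.17/10,000) = 0.4 points for power.

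| Candidates × variance each | Imbalance cut-off | Size of rule, % | Coverage of rule, % | Power: baseline only, % | Power: rule, % | Power: fixed list, % | Fixed list minus rule, points |
|---|---|---|---|---|---|---|---|
| 5 × 2% | 0.05 | 4.8 | 95.2 | 82.5 | 82.7 | 85.9 | 3.2 |
| 5 × 2% | 0.20 | 4.4 | 95.6 | 82.6 | 83.1 | 86.1 | 3.0 |
| 5 × 5% | 0.05 | 4.2 | 95.8 | 82.3 | 83.3 | 92.1 | 8.8 |
| 5 × 5% | 0.20 | 3.9 | 96.1 | 82.7 | 85.8 | 92.4 | 6.5 |
| 10 × 3% | 0.05 | 4.1 | 95.9 | 81.9 | 83.0 | 93.5 | 10.4 |
| 10 × 3% | 0.20 | 3.2 | 96.8 | 82.2 | 85.3 | 93.4 | 8.1 |
| 10 × 0% | 0.05 | 5.2 | 94.8 | 83.2 | 83.0 | 82.1 | −0.9 |
| 10 × 0% | 0.20 | 5.1 | 94.9 | 82.2 | 81.9 | 81.1 | −0.8 |

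Differences were taken before rounding. The fixed list held its size in every row (4.9 to 5.3%). In extreme settings, where candidates explain a further 50% of variance (10 × 5% or 5 × 10%), the rule's size fell to between 2.1 and 3.7% and the power gap reached about 15 points.

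**4. Which condition drives this.** Imbalance does. A covariate explaining 5% of variance has an expected association statistic of √(0.05 × 338/0.95) = 4.2, so it nearly always passes the association test. Judging association from prior knowledge instead would change little.

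**5. Discretion.** If an analyst reported the smallest p-value among the baseline-only, selected and full models, size would be 6.8 to 9.2% with prognostic candidates and about 5.9% with non-prognostic ones. This is a worst case and not what the article calls for.

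**The case against.** Four points can be made for the plan.

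- **The promised power is kept.** A reader might infer that the rule undermines the 83%. It does not: with prognostic candidates it gave 82.7% or more, and with non-prognostic ones it stayed within about 0.3 points of the baseline-only model. The shortfall is against a better model that the trial never planned. This stands.
- **The rule does not inflate Type 1 error as written.** A reader might infer a false-positive risk. Followed mechanically, the rule errs the other way. Inflation requires choosing among models by p-value, which nothing in the Primary analyses section permits. The masking in the Blinding section hides which arm a choice would favour. It limits the risk but does not rule it out, because imbalance and two-sided p-values are visible with coded arms. This largely stands.
- **The larger gains rest on assumption.** An extra 25 to 30% of variance is 2.8 to 3.3 times the 9% (0.3²) that the plan credits to the baseline score. Nothing in the article shows that the other baseline measures predict the outcome. This stands, and is why a range is given.
- **A separate analysis plan may supply the candidate list and thresholds.** It may, and their absence from the article is not the complaint. But the article itself makes imbalance a condition of entry. Adding cut-offs would keep that condition, and a list applied regardless of balance would contradict it. On this the objection fails.

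**Conclusion.** The rule is poorly chosen and should be changed, but it does not invalidate the primary result. With prognostic candidates of weak to moderate strength, its true size is roughly 4 to 5% in most settings tried (lowest 3.2%, with ten candidates and a loose cut-off), and intervals are somewhat too wide. Compared with always including the same variables, it forgoes about 3 to 4 points of power at an extra 10% of variance explained, about 7 to 10 points at 25 to 30%, and nothing if the variables are not prognostic. All of this depends on assumed covariate strength, number of candidates and cut-offs. The calculations do not support a claim that the stated power fails or that the rule as written raises the false-positive rate, and they do not show bias in the treatment estimate.

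**What to change.** Remove the imbalance-driven sentence from the primary analysis. Before any outcome data are seen by arm, fix the covariates as the baseline outcome, site and a short list of variables already collected and judged prognostic on prior grounds, all included whatever their observed balance. Catastrophizing, expectation of pain relief, the comorbidity index and stenosis severity are possible candidates, but the article gives no evidence on their strength, so the choice needs its own justification. Keep imbalance-driven adjustment only as a labelled sensitivity analysis.

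The cost is one paragraph of wording and no new data. The sample size statement can stay, since it already describes the smaller fixed model. The downside is about 1 point of power if the listed variables prove not to be prognostic (ten such variables in the simulation), which is a reason to keep the list short.

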### Secondary analyses

We will conduct two subgroup analyses to assess evidence for treatment effect on the primary outcome measures within categories defined by race and injection approach (transforaminal/interlaminar). We do not hypothesize that the treatment effect will be larger or smaller in one subgroup compared to another, only that there is a significant treatment effect within each subgroup.

We will assess secondary outcomes using ANCOVA models for continuous measures and logistic regression models for binary measures. These analyses will include assessment of group differences in clinically meaningful changes in pain and function (e.g., at least a 30% improvement on the Roland Morris Disability Questionnaire and pain scores).

Secondary analyses will consider the complete time profile for the primary outcome measures of pain and function through 12 months using methods appropriate for the analysis of repeated measures. Crossover and missing data will complicate analysis of follow-up data. Long-term outcomes will be evaluated using linear mixed effects models for repeated measures in both intent-to-treat and as-treated analyses. We will tabulate crossover rates by randomized treatment arm and compare the rates using Chi-squared tests and logistic regression as appropriate. To assess the impact of crossover on the overall evaluation of ESI, we will examine longitudinal models of outcome that incorporate a time-varying covariate indicating when treatment occurred.

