A few cohort studies suggest that ESI may provide short-term pain relief [7,8]. However, the results of RCTs have been less favorable. One early RCT [9] demonstrated no advantage of ESI over saline or local anesthetic injections. However, some argue that the poor results of this trial were a consequence of inadequate technique and do not reflect the current practice of performing ESI with fluoroscopic guidance to ensure appropriate placement of the steroid medication [10].

Only one RCT of fluoroscopically-guided ESI compared to injections with local anesthetic alone has been published [11]. This study, while showing improvement in each group, found no advantage of the steroid injection over an injection of local anesthetic alone [11]. However, this study suffered significant methodological limitations including lack of statistical power, no primary outcome measure, un-blinding of patients and researchers and a high dropout rate (21/60 patients).

The overall objective of this multi-center, double-blind RCT is to evaluate the effectiveness of ESI plus local anesthetic versus local anesthetic alone in improving pain and function among older adults with back pain and lumbar spinal stenosis. We hypothesize that patients randomized to receive ESI with local anesthetic will show significantly greater improvement in pain and function compared to patients randomized to receive local anesthetic only. We will also examine whether ESI is differentially effective in improving pain and function for different patient subgroups (African-Americans vs. Caucasians and patients undergoing a transforaminal vs. interlaminar approach). Finally, we will compare resource use and costs in the two treatment groups as well as incremental cost-effectiveness and incremental cost utility from both payer and societal perspectives.

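### The stated aim is differential effectiveness by race and injection approach, but the subgroup plan only tests for an effect within each category, and race is defined in two ways

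*Protocol article*

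**What the plan says.** Three places in the protocol article bear on the point.

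- **Background, last paragraph.** The aim is a contrast of effects: "We will also examine whether ESI is differentially effective in improving pain and function for different patient subgroups". The contrasts named are "African-Americans vs. Caucasians and patients undergoing a transforaminal vs. interlaminar approach".
- **Secondary analyses.** Two subgroup analyses are planned "to assess evidence for treatment effect on the primary outcome measures within categories defined by race and injection approach". The investigators expect neither category to show the larger effect; their hypothesis is "only that there is a significant treatment effect within each subgroup".
- **Sample size.** The factors are given as "race: Caucasian/non-Caucasian; approach: interlaminar/transforaminal". The subgroup analyses are powered within category, with a Bonferroni correction for two tests, and "we did not power the study for the hypothesis of a larger treatment effect within one subgroup compared to another".

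No section describes an estimate or a test that compares the treatment effect between categories.

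**The concern.** Whether ESI is differentially effective is a question about the difference between two treatment effects. A separate test in each category answers another question: whether each effect differs from zero. Two within-category p-values can fall on opposite sides of the threshold when the effects are the same, and they can both be significant when the effects differ.

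The Background tells the reader to expect an answer on differential effectiveness. If the only planned output is significance by category, a result that is significant in one category and not in the other has no planned estimate beside it to show how uncertain the difference is.

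The race contrast adds a second problem. A patient who is neither African-American nor Caucasian is outside the contrast in the Background but belongs to the non-Caucasian category in Sample size. Secondary analyses says only race, so it does not settle which applies. While both definitions stand, the choice between them can be made after results are seen.

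**Working it through.** **Inputs (all from Sample size).** Up to 400 patients, 1:1; 85% follow-up at 6 weeks; SD 7.5; baseline correlation 0.3; overall effect 2.25 points; subgroup n = 200 (100 per group) with effect 3.25 points and stated power 83%. The Bonferroni correction for two tests is read as 0.025 two-sided per category test, so z = 2.2414.

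**Formulas.** Residual SD after ANCOVA = 7.5 × √(1 − 0.3²) = 7.155. SE of a treatment effect with n evaluable per arm = 7.155 × √(2/n). Two-sided power = Φ(δ/SE − z) + Φ(−δ/SE − z), normal approximation.

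**The plan's own figures.**
- Overall: n = 0.85 × 200 = 170 per arm, SE 0.776, δ/SE = 2.90, z = 1.96. Power 82.6%; stated 83%. Reproduced.
- Subgroup: n = 100 per arm, SE 1.012, δ/SE = 3.21. Power 83.4%; stated 83%. Reproduced, but only with all 100 per arm evaluable. With 85 per arm (85% of 100), SE is 1.098 and power is 76.4%. Both sizes are carried forward as a range.

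**Chance of a split result when the true effect is the same in both categories.** The categories share no patients, so the tests are treated as independent: P(exactly one significant) = p₁(1 − p₂) + p₂(1 − p₁).

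| Evaluable per arm, categories 1 and 2 | True effect | p₁ | p₂ | P(exactly one) |
|---|---|---|---|---|
| 100 and 100 | 3.25 | 0.834 | 0.834 | 0.28 |
| 85 and 85 | 3.25 | 0.764 | 0.764 | 0.36 |
| 100 and 100 | 2.25 | 0.493 | 0.493 | 0.50 |
| 85 and 85 | 2.25 | 0.424 | 0.424 | 0.49 |
| 51 and 119 (30:70, assumed) | 2.25 | 0.257 | 0.573 | 0.54 |
| 34 and 136 (20:80, assumed) | 2.25 | 0.173 | 0.638 | 0.59 |

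The last two rows are assumptions. The article gives no expected split by race or approach; n = 200 per category implies an even one.

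**What a direct comparison could show.** With an even split and 85 evaluable per arm in each category, the SE of the difference in effects = 7.155 × √(2/85 + 2/85) = 1.55. The 95% CI half-width is 1.96 × 1.55 = 3.04 points. At two-sided 0.05, power is 0.305 for a true difference of 2.25 points and 0.553 for 3.25 points. The difference detectable with 80% power is 1.552 × (1.960 + 0.842) = 4.35 points.

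**Race definition.** No arithmetic applies. The Background names African-Americans and Caucasians; Sample size names Caucasian and non-Caucasian. The two coincide only if nobody of another race is enrolled, and no eligibility criterion makes that so.

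**The case against.** The best defence is that the Methods are consistent and open. Secondary analyses and Sample size give the same within-category hypothesis, and Sample size says plainly that an interaction was not powered. The odd one out is a single sentence in the Background. That stands, and it is why rewording that sentence is an acceptable repair.

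It can also be said that model terms for a secondary analysis belong in an analysis plan that is not shown. That stands as far as a missing interaction term goes. It does not remove the mismatch: the article states one aim and then a different hypothesis for it, and an added model term would leave both statements in place.

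The split-result probabilities depend on the inputs. On the plan's own subgroup design (100 per arm, 3.25 points) the figure is 28%, the lowest in the table. The higher values need a smaller true effect, incomplete follow-up or an uneven split.

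Three stronger readings are tempting, and the document supports none of them:

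- *The protocol rules out any comparison of subgroups.* It disclaims a hypothesis of a difference and power for one. It does not say that no comparison will be made.
- *The trial cannot answer the question.* The categories of a factor are disjoint, so the two estimates and their SEs would give the difference and its CI. What is missing is a stated intention to report it.
- *The investigators will read a split result as a differential effect.* Nothing says so; they expect an effect in each category. The risk lies in setting within-category tests beside the Background's aim.

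**Conclusion.** The concern holds as a mismatch between the stated aim and the planned subgroup tests, together with two incompatible race definitions. With equal true effects and equal categories, a split result has a probability of about 28% to 36% at 3.25 points and 49% to 50% at 2.25 points. It reaches 54% or 59% at 2.25 points if the smaller category is assumed to hold 30% or 20% of patients. Such a pattern cannot support a statement about differential effectiveness.

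These figures rest on the plan's SD and correlation, 0.025 per category test, independence of the two tests and a normal approximation. They concern the Roland-Morris score only; the article gives no sizing inputs for the pain scale.

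This should be fixed, but it does not threaten the trial's main conclusion. The subgroup analyses are secondary, and the primary six-week comparison, its alpha and its power are unaffected.

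**What to change.** Choose one of two routes.

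1. **Keep the aim.** For each subgroup factor, fit one ANCOVA on all evaluable patients with a treatment-by-subgroup term, keeping the planned adjustment for baseline score and site. Base any statement on differential effectiveness on that term's estimate and 95% CI. Report the within-category effects with their CIs alongside. State in advance that precision is low: a half-width of about 3.0 points at an even split with 85% follow-up.
2. **Change the aim.** Reword the Background to say that the effect of ESI will be estimated within each subgroup, as designed and powered, and that no claim about a difference between subgroups will be made.

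Under either route, put one race definition in the Background, Secondary analyses and Sample size, say how patients of other races are handled, and fix this before the randomization code is unmasked.

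The cost is a few sentences and, for the first route, one model term per factor. No extra patients or data are needed. The price of the first route is admitting that the trial can say little about subgroup differences of the size it was designed to detect overall.
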